7.1.1 Patient identification

Diabetes UK will refer potential participants through the Diabetes UK website to the platform where they can sign up, giving permission to share Mix panel data (including their email address), to be passed on to the lead CU researchers allowing them to contact participants as part of the wider research project. The lead CU researchers will send an invitation email to participants with enclosed Participant Information and Informed Consent Form explaining the project aim, related activities and burden in terms of duration. Once participants provided informed consent electronically, survey questions will be shown for which a reminder will be send two times to non-responders (unless they reply on the email by unsubscribe) by an automated setting through Qualtrics. The first part of the survey will verify diagnosis (e.g., Type 1, Type 2, at risk or other) and sufficient understanding of verbal/written English language would be derived from completing the consent form.

- - 1. Screening

For the current project no laboratory or diagnostic testing is involved in the above-mentioned inclusion criteria. Therefore, no specific duration between screening and recruitment is expected. Based on the current inclusion/exclusion criteria, no participants will be expected to be subject to rescreening.

7.1.3 Payment

Case study and interview participants will be offered a £10 (interview) or £20 (case study) gift voucher as a thank you for giving up their time. Survey respondents will have the opportunity to enter a prize draw to win gift vouchers (£55 per survey) as a thank you for giving up their time. It is considered that these amounts will recognise and thank participants for giving up their time to contribute to the project, and are not amounts that would encourage undue inducement.

[figure not shown]

Figure 1. Flowchart data sharing

**7.2 Consent**

Once participants signed up for the platform, giving permission to share Mix Panel data and their email address, CU lead researchers will approach participants by email and shortly inform them about the project purposes, related activities and burden in terms of duration. The participant will receive the PI, ICF and Invitation Letter by email which they can sign electronically. These materials are in compliance with GCP guidelines, local regulatory requirements and legal requirements. Participants will have one week before they receive a reminder email, which is seen as an adequate amount of time given to decide if they want to participate or not. Participants will also be offered the possibility to ask additional questions regarding their participation in the current project.

It is important to stress that participants have a free choice to participate in the current project. The participant has the right to refuse participation and withdraw at any time without giving reasons why they do not want to participate. This will not influence his/her current or further participation in programmes delivered by Diabetes UK or platform developer. Participants will be informed that they may withdraw any time until the point that their data is anonymised for analysis, this will be two weeks after data collection took place. At this point the researchers will not be able to identify their data for withdrawal. CU lead researchers have to ensure that in case re-consent (or in case new information) is required this is done in a timely manner. All participants are required to sufficiently understand verbal/written English language. Participants will provide electronically signed informed consent as they are expected to have sufficient understanding to give full consent to participate in the current project independently.

**7.3 Randomisation scheme (if applicable)**

Not applicable.

**7.4 Baseline data**

For the current project, no data will be collected at baseline apart from data concerning inclusion/exclusion criteria, sociodemographic data, digital literacy, general health status, diabetes related health, confidence in meal planning, expectations regarding the platform, healthy eating. This will all be included in the first survey distributed through Qualtrics software.

**7.5 Trial assessments**

7.5.1 Descriptive and Inferential data analyses

Descriptive and inferential (where possible) analyses will be performed in IBM SPSS software (version 26) on health and intervention outcomes collected through survey and Mixpanel data. The survey will assess sociodemographic (e.g., diagnosis, age, gender, ethnicity, educational status, digital literacy) variables, health outcomes and will ask for expectations regarding the platform beforehand and satisfaction afterwards. Participants will be compared on health outcomes before and after the use of the platform to see if there are differences in health outcomes (e.g. weight, length, HbA1c, blood pressure, waist, generic health status, smoking yes/no) over time. Descriptive data of session frequency, session duration, pages visited, health score for recipes used on the platform as derived from Mixpanel will also be requested from platform developer to get insight into platform usage and support the selection of case studies. For Diabetes UK this will focus on traffic to site and referrals. Sub-group (or moderator analyses) according to expectations, age, ethnicity, diagnosis, digital literacy and sex will be conducted to examine possible differences in intervention and health outcomes. Data will be analysed using IBM SPSS Software, generating descriptive and inferential statistics with reported effect size, if data availability/quality allows.

7.5.2 Case study interviews

The project will include four case studies to gain a deeper understanding of the issues and challenges platform users encounter whilst using the platform and related education offered by Diabetes UK. The project team aims to include a variety of users for these case studies ranging from younger and older service users, British, Asian, Black, Mixed and other backgrounds but also in terms of intervention engagement (low versus high users). Where possible, the platform developer will provide data on hotspot analysis to guide the questions and key areas of the platform to look at. Preferred case studies will be identified with support from Diabetes UK. The case studies will give insight into how people use and engage with the platform (also during COVID-19 restrictions), and the factors contributing to platform engagement but also gives understanding to which platform elements could be improved. After obtaining ethical permission and informed consent, each selected case study will be interviewed individually and in-depth via online screen-sharing software (or telephone if preferred) for up to 1.5 hours. This will be video recorded through Microsoft Teams and audio-taped for back-up purposes. Participants will receive a gift voucher of £20 to thank them for giving up their time.

7.5.3 Online semi-structured interviews

Online semi-structured interviews (supported by individual telephone interviews where required) with relevant stakeholders: Online interviews will last between 30 minutes and 1-hour, utilising Microsoft Teams software which contains screen-sharing and recording options stored in Microsoft Stream. The screen sharing option is specifically useful to ensure understanding between researcher and participant when discussing specific aspects of the platform. Participants who are not comfortable with an online conversation will be offered a traditional telephone interview. In total, it will be anticipated to conduct 24 interviews with (1) Platform developer, Diabetes UK staff members; and (2) Platform users with a variety of sociodemographic characteristics as identified from survey results and usage patterns as identified from Mix panel. Results of these online interviews will be transcribed verbatim and thematically analysed (based on Thematic Analysis). Where possible, the platform will provide data on hotspot analysis to guide the questions and key areas of the platform to look at. Questions will also be developed to explore in more detail the findings of the survey. Key themes from the analysis will be presented in the interim and final reports. Interviews will be conducted until “theoretical saturation” is reached – the point where no new concepts emerge from interviews. Considering the variety of sociodemographic and type of diabetes to be included in the project, it is anticipated that this could be approximately 24 users, from which 4 are platform staff members and 4 are Diabetes UK dieticians. Participants will receive a gift voucher of £10 to thank them for giving up their time.

7.5.4 Surveys

Survey to all platform users invited to use the platform and familiar with Diabetes UK ecosystem: An online survey taking a maximum of 20 minutes to complete (hosted by Qualtrics) will be sent to all service users who were referred by Diabetes UK to use the platform and examine their user experience and possible difference in perceptions towards Diabetes UK. This survey will contain questions about expectations at study commencement, usefulness, satisfaction and ease of use, as well as exploration of reasons for how often they use the platform recipes (also during COVID-19 restrictions), as this may differ from tracked platform usage as captured by Mixpanel (e.g. if they printed off their recipes upon first login, therefore had no need to login to the platform again). The survey will include an adapted version of the System Usability Scale. Survey results will be exported to and coded using IBM SPSS software and described using descriptive statistics according to sociodemographic characteristics (e.g. ethnic group, age, digital literacy, educational level, diagnosis and sex) where possible. Participants will be entered into a gift voucher prize draw (to win a prize of £55) to thank them for giving up their time.

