8.3.2 Primary outcome analysis

Participants will be analysed on health outcomes before and after they used the platform to see if there is an improvement within this group over time. These data will be analysed using IBM SPSS software (version 26) generating descriptive and inferential statistics with reported effect size (if data availability/quality allows). Descriptive data of platform usage (e.g. session frequency, session duration, pages visited, health score for recipes used) will also be provided by the platform developer through Mix panel. These data will be exported into IBM SPSS software (version 26) and will be used to select participants with different engagement levels (low vs. high) for participation in case studies and semi-structured interviews. Where possible descriptive data of platform usage will be related to health outcomes. Results of the case study interviews and semi-structured interviews will be transcribed verbatim and thematically analysed (based on Grounded Theory) resulting in overall key themes. Survey results will be exported to and coded using IBM SPSS software (version 26) and described using descriptive statistics (e.g. frequencies, percentages, medians and means) according to sociodemographic characteristics (e.g. ethnic group, age, digital literacy, educational level, diagnosis and sex).

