**System Usability Scale**

1. How often did you use the platform in the eight week period?

□ never

□ approximately once a month

□ approximately once a week

□ couple of times a week

□ every day

1. How many minutes did you use the platform approximately per session?

_____________ hours _____________ minutes

[figure not shown]

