10. The platform is easy to use / user-friendly

| 1 – Very Strongly disagree | 2 | 3 | 4 | 5 – Neither agree nor disagree | 6 | 7 | 8 | 9 | 10 – Very strongly agree |
| --- | --- | --- | --- | --- | --- | --- | --- | --- | --- |
|  |  |  |  |  |  |  |  |  |  |

Please explain your rating _________________________

11. Would you recommend the platform to other people who have Diabetes or are taking care of people with Diabetes?

□ Yes, please explain your answer _________________________

□ No, please explain your answer _________________________

12. How motivated were you to use the platform?

| 1 – Not very motivated | 2 | 3 | 4 | 5 – Neither unmotivated nor motivated | 6 | 7 | 8 | 9 | 10 – Very motivated |
| --- | --- | --- | --- | --- | --- | --- | --- | --- | --- |
|  |  |  |  |  |  |  |  |  |  |

Please explain your rating _________________________

13. Based on your experience, how would you rate the platform overall? (1=not good at all, 10 = very good)

| 1 | 2 | 3 | 4 | 5 | 6 | 7 | 8 | 9 | 10 |
| --- | --- | --- | --- | --- | --- | --- | --- | --- | --- |
|  |  |  |  |  |  |  |  |  |  |

14. Would you like to continue using the platform?

□ Yes, please explain your answer _________________________

□ No, please explain your answer _________________________

15. Do you think COVID-19 restrictions have been affecting optimal usage of the platform?

□ Yes, please explain your answer _________________________

□ No, please explain your answer _________________________

16. What would you improve to the platform?

………………………………………………………………………………………………………………………………………………………………………………………………………………………………………………………………………………………………………………………………………………………………………………………………............................................................................................................................................................................................................

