## To start…

1. What made you think it would be useful to use/take part?
2. How often did you use the platform?
3. How often did you use the cooking recipes?
4. How often did you use the shopping list activity?

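### The second survey omits the recipe-use question that Section 7.5.4 relies on to catch printed recipes, so offline users cannot be identified systematically

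*Combined protocol and SAP*

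**What the plan says.** Section 7.5.4 lists the survey's content and includes "exploration of reasons for how often they use the platform recipes". It gives the reason: recipe use may not match tracked usage, for example "if they printed off their recipes upon first login, therefore had no need to login to the platform again".

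The second survey (Attachment 6) has two usage questions under the System Usability Scale heading: "How often did you use the platform in the eight week period", with five answers from never to every day, and "How many minutes did you use the platform approximately per session". Under Satisfaction it asks "Do you think COVID-19 restrictions have been affecting optimal usage of the platform", with room to explain. The case-study outline (Attachment 10) asks "How often did you use the cooking recipes".

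Section 8.3.2 puts Mixpanel usage data to two uses. One is choosing low and high engagers for the case studies and interviews. The other is analytic: "Where possible descriptive data of platform usage will be related to health outcomes".

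**The concern.** The protocol itself names a fault in its exposure measure and names the survey as the place where the fault will be covered. If the instrument is fielded as attached, that cover is missing. Someone who prints recipes on day one and cooks from them for eight weeks leaves little trace in session counts, and can truthfully report little platform use in the survey.

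What is at stake is the reading of any relation between usage and health outcomes. A weak relation could mean that using the recipes does little, or that some regular recipe users were recorded as barely exposed. The planned data could not separate the two. Section 7.6 ends data collection with the last second survey, so the information cannot be recovered from that instrument afterwards.

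**Working it through.** The documents give no figure on this point, so there is nothing to reproduce. The check sets the announced content against the instruments.

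**1. What is announced.** Section 7.5.4 describes one survey but covers both expectations (first survey) and satisfaction (second survey), so both must be searched. It promises the reasons for frequency of recipe use. Reasons for a frequency presuppose that the frequency is known, and the stated rationale is that this frequency may differ from Mixpanel.

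**2. Items on recipe-use frequency, or on printed or offline use, in the legible text.**

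| Instrument | Items | Nearest content |
| --- | --- | --- |
| First survey (Attachment 4) | 0 | Printer questions in the computer-proficiency scale, which concern skill and not recipes |
| Second survey (Attachment 6) | 0 | Platform frequency, time per session, effect of COVID-19 on platform usage |
| Case-study outline (Attachment 10) | 1 | Explicit recipe-frequency question, 4 participants |
| Semi-structured outline (Attachment 14) | 0 | Open prompt on how the platform was used |

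Section 8.1 anticipates 200-300 survey participants. The one explicit question reaches 4 people, so it cannot supply a covariate for the survey analysis.

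**3. Whether the nearest item substitutes.** Take two illustrative users who each log in once and open the same recipes. User A prints them and cooks from them for eight weeks. User B never cooks one.

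| Measure | User A | User B |
| --- | --- | --- |
| Mixpanel sessions | 1 | 1 |
| Mixpanel recipes viewed | same | same |
| Survey: platform frequency | low | low |
| Recipes actually cooked | regular | none |

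The platform-frequency item gives the same answer for both, so it repeats the blind spot. Print is listed among the Mixpanel actions in Section 3.2, but under in-store shopping, and a print event would not show whether anything was cooked.

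**4. Where it enters the analysis.** The primary analysis in Section 8.3.2 compares the same people before and after. It needs no usage variable and is untouched. The usage-outcome relation in the same section does need one, and there user A may be treated as low-exposure.

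**The case against.** The strongest reply is that offline users need not end up as low users. The plan gives no cut-off or defining measure for low and high engagement. Mixpanel records more than logins: Section 3.2 also counts recipes opened and stored and meal plans made. A person who opened and printed many recipes in one sitting could score low on sessions but high on recipes viewed. This stands. A reader might infer that printed-recipe users are definitely counted as low users; the documents support only that they may be.

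A reader might also want a percentage for the dilution. If a fraction m of a low group had the high-group mean, the difference would shrink by the factor (1 - m). But the documents give no m, and they plan no high-versus-low comparison of health outcomes; the split is used only to choose interviewees. Any such figure would restate its own assumption.

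Other routes may bring offline use to light: free-text explanations in the second survey, the COVID-19 question, and the semi-structured interviews, which open broadly and add questions based on survey answers. Interviewing an apparent low user who turns out to cook from printouts would be informative, so the harm to interview selection is modest. All this is fair, but these routes are incidental and give no measure for each participant.

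Finally, the figure that follows the two usage questions in Attachment 6 is not shown. It probably holds the usability scale, but that cannot be confirmed.

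**Conclusion.** The mismatch between Section 7.5.4 and Attachment 6 is real, subject to the one figure that cannot be checked. Offline recipe use cannot be identified systematically from the planned data, and such users may be misclassified as low-exposure in the usage-outcome analysis.

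The size cannot be derived: the documents give neither the share of offline users nor their outcomes. If they benefit much as frequent users do, the effect would be to weaken the observed relation, but that is an assumption. It would be too strong to say that the project's main result is compromised. What is affected is a secondary analysis, conditional on feasibility, in an exploratory project without hypotheses. The change is still worth making before the second survey goes out, because it is cheap and supplies what the protocol already says it needs.

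**What to change.** Add to Attachment 6, beside the two usage questions: *In the past 8 weeks, how often did you cook a recipe from the platform, including ones you printed or saved?* Offer never / about monthly / about weekly / several times a week / daily, followed by an open line asking why.

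State in Section 8.3.2 that this item is used alongside Mixpanel counts as an exposure measure when usage is related to health outcomes. The item alone changes nothing unless the analysis uses it.

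Use it for the low/high interview selection only where selection takes place after the second survey. Section 7 bases selection on usage data and on consent given at the end of the first survey, so people chosen earlier cannot be classified by an item asked at eight weeks.

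The cost is one or two more items. The measure is self-reported and will be missing for second-survey non-responders. Section 7.5.4 sets a 20-minute maximum but no completion time is given for the present second survey, so the fit should be checked when the form is tested.

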## **7.6 End of Project definition**

Data collection will end once the last participant completed the *after* survey. The project will end after the final report has been submitted to WMAHSN (estimated after a 12 months period).

# 8. STATISTICS AND DATA ANALYSIS

**8.1 Sample size calculation**

The current project consists of platform usage data (collected through Mixpanel), *before* and *after* surveys (anticipated n= 200-300), case studies (n=4) and online semi-structured interviews (n=24). Sample size is not derived statistically but based on the exploratory nature of the project and qualitative case study / interview set-up.

**8.2 Planned recruitment rate**

The planned recruitment rate for case study interviews is four participants and 24 participants for the online semi-structured interviews depending on the availability of platform developer staff (n=3) and Diabetes UK dieticians (n=3). All participants (anticipated n=200-300) will be approached to fill in a *before* and *after* survey. Overall, it is expected that more participants will be approached than mentioned above as nonresponse should be taken into account.

- 1. **Statistical analysis plan**

8.3.1 Summary of baseline data and flow of patients

These baseline data consist of height, weight, waist, BMI, blood pressure, Hba1c, sex, ethnicity, religion, employment status, sexual orientation, accommodation status, disability status, smoking status and general health status and expectations regarding the platform.

8.3.2 Primary outcome analysis

Participants will be analysed on health outcomes before and after they used the platform to see if there is an improvement within this group over time. These data will be analysed using IBM SPSS software (version 26) generating descriptive and inferential statistics with reported effect size (if data availability/quality allows). Descriptive data of platform usage (e.g. session frequency, session duration, pages visited, health score for recipes used) will also be provided by the platform developer through Mix panel. These data will be exported into IBM SPSS software (version 26) and will be used to select participants with different engagement levels (low vs. high) for participation in case studies and semi-structured interviews. Where possible descriptive data of platform usage will be related to health outcomes. Results of the case study interviews and semi-structured interviews will be transcribed verbatim and thematically analysed (based on Grounded Theory) resulting in overall key themes. Survey results will be exported to and coded using IBM SPSS software (version 26) and described using descriptive statistics (e.g. frequencies, percentages, medians and means) according to sociodemographic characteristics (e.g. ethnic group, age, digital literacy, educational level, diagnosis and sex).

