3.2 Primary endpoint/outcome

The primary outcomes are categorized as follows: (1) Outcomes directly related to the health status and condition management of the participants (e.g. weight, BMI, HbA1c, blood pressure, waist, generic health status, smoking yes/no, confidence in diabetes management and meal planning, healthy eating) and (2) Outcomes directly related to platform intervention usage:

- Number / Duration of sessions
- Number of users / average sessions per user
- New users
- Monthly Active Users / Weekly Active Users
- Specific actions:
  - # Recipes Viewed, (any indication on favourite content)
  - # Recipe Added / Saved
  - # Meal Plans created
  - # Shopping Actions
    - Carts sent online
    - Meal plans sent to cart
    - In store shopping actions - print, email, sms, app, etc.
    - Number of items shopped / value
- Platform used - app vs web app
- GA audience metrics: Demographics, Geography,
- User Retention
- Top 20 recipes (potentially)
- The average or typical meal plan including health score (potentially)

Additionally, expectations beforehand and satisfaction afterwards will be assessed. Diabetes UK will collect data regarding their traffic on the website and the amount of referrals to the online platform.

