**Diabetes Related Health Status**

1. We would like to know your height. Would you like to answer in imperial (feet, inches) or metric (metres, centimetres) units? Please specify date DD/MM/YYYY.

□ Imperial (feet, inches)

□ Metric (metres, centimetres)

[Based on answer skip to drop down menus to select height in preferred units]

1. **How was this height measured:** (if other please specify)

□ Myself

□ Doctor

□ Other, please specify_________________________

□ Don’t know

□ Prefer not to say

1. We would like to know your weight. Would you like to answer in imperial (stones, pounds) or metric (kilograms) units? Please specify date DD/MM/YYYY.

□ Imperial (stones and pounds)

□ Metric (kilograms)

[Based on answer skip to drop down menus to select weight in preferred units]

1. **How was this weight measured:** (if other please specify)

□ Myself

□ Doctor

□ Other, please specify_________________________

□ Don’t know

□ Prefer not to say

1. We would like to know your waist size. Would you prefer to answer in imperial (inches) or metric units (centimetres)? Please specify date DD/MM/YYYY.

□ Imperial (inches)

□ Metric (centimetres)

[Based on answer skip to drop down menus to select waist size in preferred units]

[figure not shown]
Above the belly button, just below the rib cage. Bend to one side to find natural crease of your waist. Measure across at this point.

1. **How was this waist size measured:** (if other please specify)

□ Myself

□ Doctor

□ Other, please specify_________________________

□ Don’t know

□ Prefer not to say

1. What is your most recent blood glucose (sugar) level? (HbA1c mmol/mol)

□ Don’t know

□ Prefer not to say

1. What is the date of your most recent blood glucose level measurement?

DD/MM/YYYY

□ Don’t know

□ Prefer not to say

1. What is your most recent blood pressure level?

Systolic (top number) mmHg [drop down menu – 70, 80, 90, 100, 110, 120, 130, 140, 150, 160, 170, 180, 190]

Diastolic (bottom number) mmHg [drop down menu – 40, 50, 60, 70, 80, 90, 100]

□ Don’t know

□ Prefer not to say

1. What was the date of your most recent blood pressure level?

DD/MM/YY

□ Don’t know

□ Prefer not to say

1. What was your most recent HDL cholesterol level (mmol/L)?

[drop down menu]

□ Don’t know

□ Prefer not to say

1. What was your most recent TOTAL cholesterol level?

______________ mmol/L [drop down menu]

□ Don’t know

□ Prefer not to say

1. What is the date of your most recent cholesterol measurement?

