**Diabetes Related Health Status**

1. We would like to know your height. Would you like to answer in imperial (feet, inches) or metric (metres, centimetres) units? Please specify date DD/MM/YYYY.

□ Imperial (feet, inches)

□ Metric (metres, centimetres)

[Based on answer skip to drop down menus to select height in preferred units]

1. **How was this height measured:** (if other please specify)

□ Myself

□ Doctor

□ Other, please specify_________________________

□ Don’t know

□ Prefer not to say

1. We would like to know your weight. Would you like to answer in imperial (stones, pounds) or metric (kilograms) units? Please specify date DD/MM/YYYY.

□ Imperial (stones and pounds)

□ Metric (kilograms)

[Based on answer skip to drop down menus to select weight in preferred units]

1. **How was this weight measured:** (if other please specify)

□ Myself

□ Doctor

□ Other, please specify_________________________

□ Don’t know

□ Prefer not to say

1. We would like to know your waist size. Would you prefer to answer in imperial (inches) or metric units (centimetres)? Please specify date DD/MM/YYYY.

□ Imperial (inches)

□ Metric (centimetres)

[Based on answer skip to drop down menus to select waist size in preferred units]

[figure not shown]
Above the belly button, just below the rib cage. Bend to one side to find natural crease of your waist. Measure across at this point.

1. **How was this waist size measured:** (if other please specify)

□ Myself

□ Doctor

□ Other, please specify_________________________

□ Don’t know

□ Prefer not to say

1. What is your most recent blood glucose (sugar) level? (HbA1c mmol/mol)

□ Don’t know

□ Prefer not to say

1. What is the date of your most recent blood glucose level measurement?

DD/MM/YYYY

□ Don’t know

□ Prefer not to say

1. What is your most recent blood pressure level?

Systolic (top number) mmHg [drop down menu – 70, 80, 90, 100, 110, 120, 130, 140, 150, 160, 170, 180, 190]

Diastolic (bottom number) mmHg [drop down menu – 40, 50, 60, 70, 80, 90, 100]

□ Don’t know

□ Prefer not to say

1. What was the date of your most recent blood pressure level?

DD/MM/YY

□ Don’t know

□ Prefer not to say

1. What was your most recent HDL cholesterol level (mmol/L)?

[drop down menu]

□ Don’t know

□ Prefer not to say

1. What was your most recent TOTAL cholesterol level?

______________ mmol/L [drop down menu]

□ Don’t know

□ Prefer not to say

1. What is the date of your most recent cholesterol measurement?

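### Both surveys record who measured weight, waist and height, but the second survey does not ask for the same method and the before/after analysis does not use the item

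*Combined protocol and SAP*

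**What the plan says.** Section 3.2 lists "weight, BMI, HbA1c, blood pressure, waist, generic health status" among the primary health outcomes.

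The first survey (Attachment 4) and the second survey (Attachment 6) ask for height, weight and waist with a date. Each value is followed by a source item such as "How was this weight measured" or "How was this waist size measured". The options are Myself, Doctor, Other, Don't know and Prefer not to say. The wording is the same in both surveys, and nothing in the second refers the participant back to the method used in the first.

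Section 7.5.1 states: "Participants will be compared on health outcomes before and after the use of the platform to see if there are differences in health outcomes" [...]. Section 8.3.2 states: "Participants will be analysed on health outcomes before and after they used the platform to see if there is an improvement within this group over" [...]. It then describes the SPSS output as "generating descriptive and inferential statistics with reported effect size (if data availability/quality allows" [...]. Neither section names measurement source as a covariate, restriction, stratum or sensitivity analysis. Source is not among the moderators in 7.5.1 or 8.4. Section 8.6, whose title covers missing or spurious data, deals only with the recording of interviews and withdrawal from them. Section 8.5 keeps in the analysis everyone who took part, apart from withdrawals and people who did not share their usage data.

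**The concern.** A participant may report a clinic weight at the first survey and a home weight 8 weeks later, or the reverse. The difference then mixes any real change with a change of scale, clothing or measurer. In a randomised comparison a drift of this kind would tend to affect both arms alike. Here there is one group, so any net drift goes straight into the estimated improvement.

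Height matters as well. The surveys ask for height and weight but not for BMI, so BMI has to be derived from them. Height is asked again at the second survey, so a different height value changes BMI even when weight is constant.

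The project informs a decision on a business case and further roll-out. The item that would show whether this happened is already collected twice, but the plan does not say what to do with it.

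**Working it through.** **What can be reproduced.** The plan gives no figure to reproduce. Section 8.1 anticipates 200 to 300 survey participants and says this number is not statistically derived. No SD, target effect, switching rate or doctor-minus-self difference is given. What follows is an illustration only.

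**Set-up.** Let d be the systematic doctor-minus-self difference in weight, p1 the share switching from doctor to self, and p2 the share switching from self to doctor. A doctor-to-self pair carries an error of −d, a self-to-doctor pair +d, and a same-source pair 0. Then:

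- size of the false mean change = d × |p1 − p2|
- added variance per pair = d² × [(p1 + p2) − (p1 − p2)²]
- SE of mean change = √{(SD² + added variance) / n}

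**Assumed inputs.** Total switching p1 + p2 = 30%; d = 0.5 to 2 kg; SD of weight change 3 to 5 kg; n = 200 to 300 complete pairs; two-sided 5% paired test with no true change.

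| Net one-way switching | False mean change | Chance of a false-positive result |
|---|---|---|
| 0% | 0 kg | 5% |
| 10% | 0.05 to 0.20 kg | 5.2% to 19% |
| 20% | 0.10 to 0.40 kg | 5.9% to 59% |
| 30% | 0.15 to 0.60 kg | 7.1% to 91% |

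**A case inside the range.** With d = 1 kg, net switching 20%, SD 3 kg and n = 200:

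- false change = 1 × 0.20 = 0.20 kg
- SE = √{(9 + 1 × (0.30 − 0.04)) / 200} = 0.215 kg
- ratio = 0.20 / 0.215 = 0.93 standard errors, giving a false-positive rate of about 15%

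**Noise alone.** Take balanced switching with the largest assumed difference (d = 2 kg) and the smaller SD (3 kg), at n = 200. The SE is √{(9 + 4 × 0.30) / 200} = 0.226 kg, against √(9/200) = 0.212 kg without switching. That is about 6% more, and the mean is unbiased.

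**Cost of restricting to same-source pairs.** If 30% switched, 200 pairs become 140 and 300 become 210. The confidence interval widens by 1/√0.7 = 1.20. With an SD of 3 kg and n = 200, the 95% half-width goes from 0.42 to 0.50 kg. Leaving out unknown sources and second values dated before the first survey would reduce the pairs further, by an amount the documents do not allow one to estimate.

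**BMI.** BMI is weight divided by height squared, so a small relative difference in reported height enters BMI at about twice its size, with the opposite sign. Using one height at both times removes this.

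**The case against.** The strongest reply is that the plan is silent, which is different from choosing to disregard source. Section 8.3.2 names no test or model for any outcome and makes inference conditional on data availability and quality. That clause leaves room to act on a quality item the team chose to collect. This stands: a reader might infer that the sponsor decided to ignore source, and the text does not show that. But the clause sets no rule, so the choice would be made after the data are seen.

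Second, bias in the mean needs both a systematic source difference and net one-way switching, and the documents show neither. This also stands. A reader might infer that any reported improvement in weight or waist would be an artefact of the measurer; the documents do not support that.

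Third, both surveys give the same instruction on where to place the tape, so self-measured waist is standardised for position. This stands too. What remains for waist is a clinic value not taken under that instruction.

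Fourth, the illustration assumes 200 to 300 complete pairs, while 8.2 expects nonresponse. With 100 pairs, the case of d = 1 kg, net 20% and SD 3 kg has an SE of √(9.26/100) = 0.304 kg. The 0.20 kg shift is then 0.66 standard errors and the false-positive rate about 10%. The shift itself does not depend on n.

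Finally, one might want same-source pairs as the main analysis. That would select participants on a second-survey answer and depart from 8.5. It could also keep pairs where both answers are Don't know, or where an old clinic value was entered twice. The restriction belongs in a sensitivity analysis.

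**Conclusion.** The gap is real and modest. Source is recorded at both surveys, the second survey does not ask for the same method, and no analysis section uses the item. In this single-group design, switching adds noise to the change in weight, BMI and waist. It biases the mean change if it is mainly one-way and the sources differ systematically.

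The size cannot be computed from the documents. The range of 0 to 0.60 kg for false mean weight change rests wholly on the assumed switching shares and source difference; the false-positive rates also depend on the assumed SD and number of pairs. No corresponding figure can be given for waist or BMI.

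The point does not show that the before/after result will be wrong. Nor would the repair allow a change to be attributed to the platform, which an uncontrolled comparison cannot do. It does not reach HbA1c or blood pressure, which are asked with a date but no source item. It is worth acting on because the needed items are already collected and the cost is small.

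**What to change.** 1. In the second survey, add a line asking for a new, dated weight and waist measurement taken, where possible, in the same way as at the first survey.
2. In 8.3.2, keep all pairs as the main comparison, in line with 8.5. Tabulate source at the first survey against source at the second, for weight and for waist. Add a sensitivity analysis limited to pairs with the same known source (Myself at both, or Doctor at both) and a second measurement dated after the first survey was completed. Treat Other, Don't know and Prefer not to say as not matched.
3. For BMI, use one height per person, the first-survey value, at both time points.

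The cost is one survey line, a few sentences in 8.3.2, a little more analysis on items already collected, and fewer pairs in the sensitivity analysis. Two self-measurements on different scales would still count as matched, so the analysis reduces the problem without removing it. If second surveys have already gone out, steps 2 and 3 can still be applied.
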